
#### Experimental group

2.2.2

The experimental group will receive the SAF-T intervention in addition to the standard care provided to the control group. The SAF-T intervention was developed by the research team following an extensive review of the literature. The team comprises ICU clinicians, specialized ICU nurses, and psychiatrists and psychologists, all of whom possess substantial clinical expertise. The detailed SAF-T intervention script is provided in Table 2. Before the commencement of the formal study, to ensure the standardized implementation of the intervention, a clinical psychotherapist from the intervention development team provided SAF-T training to another researcher in the study team with EMDR learning experience. The training covered the theoretical framework and specific procedures of SAF-T, as well as the instruction of relevant psychological intervention techniques. The training process is monitored by all members of the intervention-constructed team. To ensure the consistency of the SAF-T intervention protocol, the psychological intervention will be delivered by a fixed, dedicated research member. Following each session, the interventionist will complete a session checklist to document adherence to the specific operational procedures. To proactively monitor participant well-being, the interventionist will conduct structured inquiries at the beginning and end of each session using a combination of open-ended and closed-ended questions. Throughout the session, the interventionist will remain vigilant for signs of emotional deterioration, such as crying, agitation, reduced verbal output, or expressions of hopelessness. Should such signs emerge and significantly impede the session’s progress, the intervention will be paused temporarily. The interventionist will then provide support, ensure the participant’s immediate stability, and respectfully inquire about their willingness to continue. If resumption is not feasible, the session will be rescheduled. Furthermore, participants are explicitly informed that they may pause or withdraw from the intervention at any time due to emotional discomfort without any penalty or consequence.

**Table 2 tab2:** SAF-T intervention script.

Component	Description
Objective	To alleviate stress, anxiety, and depression in ICU patients’ family members via SAF-T, empowering them for independent stress management. Skill application is encouraged based on personal relevance, not mandated.
Participants	Eligible family members of ICU patients meeting inclusion/exclusion criteria.
Duration	15–20 min/session for 3 consecutive days.
Location	Quiet, comfortable conversation room.
Intervention process	1. Pre-intervention: Schedule session; obtain informed consent; collect baseline data. 2. Intervention Sessions: ① Introduction/Review: Explain purpose and build trust/Review the previous homework and practical work situation. (About 3 min) ② Stress source identification: Link stress responses to ICU-related factors. (About 3 min) ③ SAF-T: Sit facing the subject, place your hand within their line of sight, and perform rapid parallel sliding for 1 min. Moving left to right counts as once, and right to left as twice, repeating for at least 40 cycles per minute. Keep arm swing within 90°. The subject should keep their head still, follow the researcher’s finger movement with their eyes only, and maintain slow, rhythmic deep breathing. The detailed SAF-T intervention procedures can be found in supplement 1. (About 10 min) ④ After the SAF-T: Collect participant feedback and complete the session checklist for this case. (About 4 min) ⑤ Practice & Generalization: If the participant is willing, sessions on Days 2 and 3 will focus on independent practice; discuss real-life application after final session. 3. Follow-up: Assessments at 3, 30, 90 days post-intervention and within 24 h after ICU discharge via outpatient/phone/online.

### Outcomes

2.3

#### Primary outcome and endpoint

2.3.1

The primary outcome of this trial is the psychological distress level of family members at the primary endpoint, which is defined as Day 3 (immediately after the completion of the SAF-T intervention).

#### Secondary outcomes

2.3.2

The secondary outcomes of this study focus on the trajectories of individual symptoms. To investigate the sustained and evolving effects of the intervention, individual scores for stress, anxiety, depression, PTSD, and sleep quality will be analyzed across a complete longitudinal time series. This series includes assessments at baseline (Day 1), immediately post-intervention (Day 3), within 24 h after the patient’s discharge from the ICU, and at the 30-day and 90-day follow-ups.

### Measuring tools

2.4

(1) This study will employ the PSS-10 to assess the stress levels of family members of patients in the ICU, as previous research has demonstrated that the PSS-10 exhibits superior reliability and structural validity in practical applications within China (Huang et al., 2020).(2) GAD-7 will be utilized to evaluate the anxiety levels among family members (Spitzer et al., 2006).(3) PHQ-9 will be utilized to evaluate the depression levels among family members (Williams et al., 2005).(4) PTSD Symptoms: The impact of IES-R questionnaire will be utilized to assess the severity of PTSD among family members (Horowitz et al., 1979).(5) Sleep quality: The Pittsburgh PSQI will be utilized to assess the sleep quality of family members at all-time points (Buysse et al., 1989).

### Data collection

2.5

We will use the general information questionnaire to collect demographic characteristics of patients and their families. The general information questionnaire was designed by the researchers themselves based on extensive literature reading, which included pertinent data related to ICU patients and their families, and consisted of a total of 17 items.

To address information bias arising from inter-collector variability, standardized paper-based questionnaires will be administered by data collectors after first obtaining informed consent from family members. Baseline data will first be gathered on-site. Subsequently, follow-up data collection will be carried out by pre-designated data collectors at predetermined intervals following the intervention. Data collection will primarily be conducted via telephone interviews. It will occur at pre-specified time points: on the Day 1 (pre-intervention), on the Day 3 (post-intervention), within 24 h post-discharge, as well as on the Day 30 and Day 90. Additionally, ICU discharge follow-up data will be gathered within 48 h on both the 30th and 90th study days (Table 3).

**Table 3 tab3:** Key variables, measures, and data collection time points.

Outcomes	Measures	Data collection time points				
		Study Day 1	Study Day 3	≤24 h post-ICU discharge	Study Day 30	Study Day 90
Anxiety	GAD-7	**√**	**√**	**√**	**√**	**√**
Depression	PHQ-9	**√**	**√**	**√**	**√**	**√**
PTSD	IES-R	**√**	**√**	**√**	**√**	**√**
Pressure	PSS-10	**√**	**√**	**√**	**√**	**√**
Sleep quality	PSQI	**√**	**√**	**√**	**√**	**√**
Demographic characteristics	General information questionnaire	**√**				

### Statistical analysis

2.6

In this study, EpiData3.1 software will be utilized for data entry, while IBM SPSS Statistics version 27.0 will be employed for data analysis.

All statistical tests were two-sided with *α* = 0.05, and *p* < 0.05 indicated significance. Categorical variables, including family member demographics, will be presented as counts and percentages and compared between groups using the *chi-square* test or *Fisher’s* exact test, as appropriate. Continuous variables will be assessed for normality using the *Shapiro–Wilk* test. Normally distributed data will be summarized as mean ± standard deviation, while non-normally distributed data will be summarized as median and interquartile range. For baseline comparisons of continuous variables, independent samples *t*-tests or *Mann–Whitney U* tests will be applied accordingly. For the intention-to-treat (ITT) analysis, missing data from participants who withdraw during the study will be handled using multiple imputation (MI). Specifically, the multiple imputation module in SPSS version 27.0 will be employed to create five complete datasets using the fully conditional specification method, with group allocation, time point, baseline scores, and demographic characteristics included as predictor variables. The imputed results will then be pooled for analysis.

Primary Outcome Analysis: The primary analysis will follow the ITT principle, including all randomized participants. The efficacy of the SAF-T intervention will be assessed by comparing the psychological distress composite score at the primary endpoint (Day 3) between the intervention and control groups, adjusting for the baseline composite score. (1) Calculation of the composite score. To ensure comparability across time points, all composite scores will be standardized using the means and standard deviations calculated from the Day 3 assessments. For each participant at Day 3, the composite score will be calculated as follows: First, for each of the three scales (PSS-10, GAD-7, and PHQ-9) administered at Day 3, the mean (
${\overset{ˉ}{x}}_{k}$
) and standard deviation (
$SD_{k}$
) will be calculated across all participants, where 
k=1,2,3
 represents the three scales, respectively. Second, for each participant 
i
, the raw score on each scale (
$x_{\mathrm{ik}}$
) will be standardized to a Z-score: 
$Z_{\mathrm{ik}}=\frac{x_{\mathrm{ik}}-{\overset{-}{x}}_{k}}{SD_{k}}$
. Finally, the three standardized scores will be summed to obtain the participant’s psychological distress composite score: 
$\text{CompositeScor}e_{i}=Z_{i,\mathrm{PSS}-10}+Z_{i,\mathrm{GAD}-7}+Z_{i,\mathrm{PHQ}-9}.$
 (2) Primary statistical model. The primary between-group comparison at Day 3 will be performed using an analysis of covariance (ANCOVA), with the Day 3 composite score as the dependent variable, experimental group as the fixed factor, and the baseline composite score as a covariate. Prior to ANCOVA, normality of residuals and homogeneity of regression slopes will be assessed. If the assumptions of ANCOVA are violated, a non-parametric alternative (e.g., Quade’s rank ANCOVA) will be applied. (3) Effect size and validation. To assess the clinical significance of the intervention effect, Cohen’s d effect size will be calculated, with *d* = 0.2 considered a small effect, *d* = 0.5 a medium effect, and *d* = 0.8 a large effect (Bartko et al., 1988). As a validation step, the theoretical standard deviation of the composite score will be computed using the variance sum theorem: 
$SD_{\text{theoretical}}=\sqrt{3+2(r_{12}+r_{13}+r_{23})}$
. where 
$r_{12}$
, 
$r_{13}$
, and 
$r_{23}$
 represent the Pearson correlation coefficients between each pair of the three scales. This theoretical value will be compared with the observed standard deviation to confirm the construct validity of the composite score. (4) Sensitivity analyses. As a sensitivity analysis, a per-protocol (PP) analysis will be conducted to evaluate the robustness of the primary ITT results. Additionally, to assess the potential impact of contamination, we will perform an analysis excluding control group participants who received protocol-prohibited psychological support during the intervention window.

Analysis of Secondary and Longitudinal Outcomes: For longitudinal analyses of secondary outcomes—including the individual trajectories of PSS-10, GAD-7, and PHQ-9 scores, as well as PSQI and IES-R scores across time points (Day 3, discharge, Day 30, Day 90)—linear mixed-effects models (LMMs) will be employed. This approach handles missing data under the missing-at-random (MAR) assumption and accounts for within-subject correlation. Separate LMMs will be fitted for each continuous secondary outcome. Each model will include: (1) Fixed Effects: Treatment group, time (as a categorical factor), the group × time interaction, and the corresponding baseline score of the outcome as a covariate. (2) Random Effects: A random intercept for each participant will be included to account for individual variability. (3) Covariance Structure: An unstructured covariance matrix will be initially specified to model the within-subject errors, with the final structure chosen based on model fit indices (e.g., Akaike Information Criterion). The group × time interaction will be the effect of primary interest, testing whether the change in the outcome over time differs between groups. If the interaction is significant, simple effects analyses (e.g., between-group comparisons at each time point) will be conducted. For the primary ITT analysis, missing outcome data at Day 3 will be handled using the Multiple Imputation (MI) method. Results from analyses on each dataset will be pooled using Rubin’s rules. For longitudinal LMMs, the full-information maximum likelihood (FIML) estimation inherent to the method will be utilized.

Handling of Multiplicity: All analyses of secondary outcomes and longitudinal trajectories are considered exploratory. Results from these analyses will be presented with point estimates and 95% confidence intervals to indicate the magnitude and precision of effects. *p*-values from these exploratory analyses will be interpreted descriptively and with caution, without formal adjustment for multiple testing, to avoid inflating Type II error rates while generating hypotheses for future research.

Additional Analyses: Intra-group changes from baseline to specific time points for normally distributed data will be assessed using paired *t*-tests, or the *Wilcoxon* signed-rank test for non-normally distributed data. And we will assess the sensitivity of the results to potential contamination by conducting exclusion analysis and reclassification analysis on the control group participants who received additional support.

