#### Sample size

2.1.2

The sample size estimation for this study was calculated based on the results of a pilot study by Cairns (2018). This pilot study was selected as a reference for several reasons: both studies involve similar populations (family members of ICU patients), comparable intervention intensity (continuous intervention over 3 days, each lasting 15–20 min), similar assessment tools and outcome indicators (key indicators in this study were selected from those that performed well in the Cairns’ study, or alternative validated tools were chosen to address its limitations), and largely aligned assessment time points (the Cairns’ study assessed on Day 1, Day 3, Day 30, and Day 90; this study additionally included an assessment within 24 h after patient discharge to better reflect the interaction between patients and their families). In the pilot study (*N* = 10; 5 per group), the effect size for the outcome of perceived stress from baseline to 90-day follow-up was Cohen’s *d* = 1.13 (95% CI: −0.21 to 2.47), based on a mean difference of 4.4 points (intervention: 23.0 ± 2.30 vs. control: 25.0 ± 5.05). This effect size represented the most conservative estimate among all follow-up time points (Day 3: *d* = 1.50; Day 30: *d* = 1.23; Day 90: *d* = 1.13). Sample size estimation for the “independent sample *t*-test” was performed in G Power3.1 sample size calculation software,^1^ and the calculation formula is as follows: 
$n={\left[\frac{Z_{\alpha /2}+Z_{\beta }}{\delta /\sigma }\right]}^{2}(Q_{1}^{-1}+Q_{2}^{-1})$
 (Faul et al., 2007; Faul et al., 2009). The parameter Settings are as follows: For the two-sided test, Cohen’s d is 1.13, Alpha is 0.05, the certainty Power (1-β) is 0.95, and the sample size is selected as N1 = N2. Finally, it was calculated that each group of the intervention study required 22 people. Considering a loss to follow-up rate of more than 20%, the minimum sample size included in each group was ultimately 28 people. When the sample size was sufficient, as many research subjects as possible were included in the study. Acknowledging the inherent variability and potential overestimation in pilot studies, we aimed for a conservative design by selecting a high statistical power to minimize the risk of Type *II* error.

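### The primary composite is standardised with post-treatment Day 3 SDs pooled over both arms, so its unit and the relative weights of its three scales depend on the treatment effect; pooled Day 1 constants would avoid this cheaply

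*Protocol article*

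**What the plan says.** The primary outcome is a composite of PSS-10, GAD-7 and PHQ-9 at Day 3, immediately after the three-day intervention. Section 2.6, part (1) of the primary outcome analysis, gives comparability across time points as its aim and says that "all composite scores will be standardized using the means and standard deviations calculated from the Day 3 assessments". For each scale the Day 3 mean and SD "will be calculated across all participants", that is, over both arms together. Then "the three standardized scores will be summed to obtain the participant’s psychological distress composite score", with no further weighting.

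Part (2) tests the Day 3 composite by ANCOVA with "experimental group as the fixed factor, and the baseline composite score as a covariate". Part (3) compares the observed SD of the composite with a theoretical value, sqrt(3 + 2(r12 + r13 + r23)).

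The protocol gives no expected effect on GAD-7 or PHQ-9, no correlations between the scales and no power for the composite. Its sample size rests on pilot perceived stress alone (section 2.1.2). Table 3 shows that all three scales are also collected on Day 1, before the intervention.

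**The concern.** Summing Z-scores gives each scale an effective weight of 1 divided by its standardising SD. If that SD is taken after treatment and over both arms, it includes the separation between the arms. The larger the effect on a scale, the larger its SD and the smaller its weight.

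Two things follow. First, the composite difference is expressed in a unit that itself moves with the treatment effect, so a value from this trial is harder to interpret or to compare with another. Second, if one scale responds far more than the others, the composite discounts the scale that carries the signal, and the primary test can lose some power. A pre-treatment reference has neither property.

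**Working it through.** **Inputs from the protocol.** 1:1 allocation and 28 per group (2.1.2); pilot perceived-stress effects of d = 1.50 at Day 3 and d = 1.13 at Day 90; the plan's own target of d = 0.7; two-sided alpha of 0.05.

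**Assumptions, because the protocol gives no figures.** Effects on GAD-7 and PHQ-9; correlation between scales 0.6; baseline-to-Day 3 correlation 0.6 unless stated; within-arm SDs equal at Day 1 and Day 3 unless stated.

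**The plan's own figure.** A two-sample t-test with d = 1.13, two-sided alpha 0.05 and power 0.95 needs 22 per group, and 22/0.8 = 27.5, so 28. This reproduces the stated size. It concerns perceived stress and not the composite, so there is no stated composite power to check against.

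**Weights.** With 1:1 allocation and within-arm SD σ, the pooled Day 3 SD of a scale with standardised effect d is σ·sqrt(1 + d²/4). Its weight relative to a within-arm SD is 1/sqrt(1 + d²/4):

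- d = 0.7: 1/sqrt(1.1225) = 0.944
- d = 1.13: 1/sqrt(1.3192) = 0.871
- d = 1.5: 1/sqrt(1.5625) = 0.800

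If all three scales have the same d, the factor is common and cancels from the ANCOVA test statistic.

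**Composite difference, baseline constants against Day 3 constants (simulated).**

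- Effects (0.7, 0.7, 0.7): −2.13 against −1.99; 1 − 1.99/2.13 = 0.066, about 7%.
- Effects (1.5, 0.2, 0): −1.73 against −1.40; 1 − 1.40/1.73 = 0.191, about 19%.

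The weight formula alone gives 1 − 0.944 = 5.6% in the first case. The simulated figure also carries sampling variation in the estimated SDs.

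**Power of the ANCOVA, 28 per arm.**

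| Effects on the three scales (SD) | Baseline SDs | Day 3 SDs |
|---|---|---|
| 0, 0, 0 (type I error) | 5.1% | 5.0% |
| 0.7, 0.7, 0.7 | 96% | 96% |
| 0.7, 0.5, 0.5 | 85.3% | 85.2% |
| 0.7, 0.35, 0.35 | 70% | 69% |
| 1.13, 0.3, 0.3 | 87% | 85% |
| 1.13, 0, 0 | 52% | 44% |
| 1.5, 0.2, 0 | 85% | 77% |

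With a baseline-to-Day 3 correlation of 0.5, the pattern (0.7, 0, 0) gives 21.6% against 19.9%. The most extreme pattern tried, (1.5, 0, 0), gives 68.7% against 55.6%, a loss of about 13 points.

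**Relaxing equal SDs.** Let the responsive scale's within-arm SD be 20% smaller at Day 3 than at Day 1. With effects expressed in Day 1 SD units, (1.13, 0.3, 0.3) gives 91% with baseline SDs and 92% with Day 3 SDs; the reversal is about 1 to 2 points. With effects expressed in Day 3 SD units the reversal is somewhat larger: 81% against 84% for the same pattern, 77% against 79% at (0.8, 0.4, 0.4), and about 40% against 45% at (1.13, 0, 0).

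**The case against.** The strongest reply is that the rule is pre-specified, uses one set of constants at both time points and computes them without reference to group, so alpha is preserved. It also gives every scale unit variance at the primary endpoint, which baseline constants do not guarantee. All of that is correct.

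The larger power losses need one scale to respond very strongly and the other two hardly at all. The hypotheses in section 1.1 expect stress, anxiety and depression all to improve. Near the plan's d = 0.7 the difference is at most about two points and usually less than one. If the responsive scale's spread narrows under treatment, Day 3 SDs do slightly better. The protocol gives neither SD, so neither direction can be excluded. The 7% shrinkage with equal effects is a common rescaling and leaves the test unchanged.

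A reader might infer from section 2.1.2 that PSS-10 is the scale that will be down-weighted, because it is the only one with cited effects. The document does not support this. It gives no pilot effects for anxiety or depression, which is not evidence that they are smaller, and the pilot had 10 participants and an interval from −0.21 to 2.47.

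Whether the constants would be recomputed in each imputed dataset or sensitivity set is not stated. An article may leave that detail to a fuller document, so it is not counted here as a fault.

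What stands is that the unit and the weights depend on the outcome, and that a pre-treatment reference is available for the same stated purpose.

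**Conclusion.** The point holds as a matter of scaling and interpretability, with a conditional effect on power. The standardising constants are post-treatment and contain the between-arm difference. The composite difference is smaller by about 7% (0.7 SD on all scales) to 19% (1.5, 0.2, 0) than on a baseline scale, and a dominant scale is down-weighted.

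For the concentrated patterns (1.13, 0.3, 0.3), (1.13, 0, 0) and (1.5, 0.2, 0), power falls by about 2 to 8 points. Only the still more extreme pattern (1.5, 0, 0) costs more. These figures rest on assumed correlations of 0.5 to 0.6 and equal within-arm SDs at the two days. With a smaller Day 3 SD on the responsive scale, the shift can be 1 to 2 points the other way, or a little more depending on the units in which the effect is fixed.

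A reader might conclude that the primary test simply loses power, or that it is invalid. Neither follows. With equal effects power is unchanged, at d = 0.7 the change is negligible, and type I error stays at 5%. This is a worthwhile, low-cost improvement to the primary endpoint and not an error that undermines it.

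**What to change.** In section 2.6, replace the Day 3 reference with Day 1: standardise PSS-10, GAD-7 and PHQ-9 at every time point with the pooled Day 1 mean and SD of all randomised participants. State that the same constants apply in every imputed dataset, in the per-protocol analysis and in the contamination-exclusion analysis. This still meets the stated aim of comparability across time points, which needs one fixed reference and not Day 3 in particular. Make the change before outcome data are examined.

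The cost is small but extends beyond that sentence. Day 3 Z-scores will no longer have SD 1, so the theoretical SD in part (3) no longer applies. Either replace it with the general variance-sum form, sqrt(s1² + s2² + s3² + 2(r12·s1·s2 + r13·s1·s3 + r23·s2·s3)), where s1 to s3 are the Day 3 SDs of the Z-scores, or drop the step. No extra data are needed, because the Day 1 scores are already scheduled in Table 3. The remaining trade-off is that a scale whose spread changes between Day 1 and Day 3 will not carry exactly equal variance at the endpoint.

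### The construct validity check on the primary composite compares a number with itself, so agreement tells nothing about validity

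*Protocol article*

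**What the plan says.** Section 2.6 of the protocol article, under Primary Outcome Analysis, builds the composite in item (1). It states that "all composite scores will be standardized using the means and standard deviations calculated from the Day 3 assessments". For each scale the Day 3 mean and SD "will be calculated across all participants, where" k indexes the three scales, so both arms are pooled. Then "the three standardized scores will be summed to obtain the participant’s psychological distress composite score".

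Item (3), on effect size and validation, continues: "As a validation step, the theoretical standard deviation of the composite score will be computed using the variance sum theorem". The formula given is SD_theoretical = sqrt(3 + 2(r12 + r13 + r23)), where the r terms "represent the Pearson correlation coefficients between each pair of the three scales". The stated purpose is: "This theoretical value will be compared with the observed standard deviation to confirm the construct validity of the composite score".

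The section names no acceptance threshold, outside reference value, factor analysis or internal-consistency statistic for this purpose. Under Analysis of Secondary and Longitudinal Outcomes it adds that "missing outcome data at Day 3 will be handled using the Multiple Imputation (MI) method".

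**The concern.** A validity check must be able to fail when the construct is absent. This one takes its two sides from the same data by the same definition, so agreement is guaranteed in advance and has no evidential value.

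The composite is specific to this study and is the only primary outcome. This step is also the only one in the article described as validating it. As written, the report would state that construct validity had been confirmed, and readers would rely on that when interpreting an equally weighted sum of stress, anxiety and depression scores. If the three scales were weakly related or responded differently to the intervention, the sum would be hard to interpret, and agreement of the two SDs would give no warning.

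**Working it through.** **Inputs, all from section 2.6.** Standardisation uses each scale's own Day 3 mean and SD, both arms pooled. The composite is an unweighted sum of three Z-scores. The correlations are the trial's own sample Pearson values. The article gives a formula for the theoretical SD and no numerical value. The planned total of 56 comes from the Abstract.

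**Algebra.**

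1. With Z_k = (x_k − mean_k)/SD_k and the mean and SD taken from the same sample, Var(Z_k) = 1 exactly.
2. For two scales, Cov(Z_j, Z_k) = Cov(x_j, x_k)/(SD_j × SD_k) = r_jk, the sample Pearson correlation.
3. Var(Z1 + Z2 + Z3) = 1 + 1 + 1 + 2(r12 + r13 + r23) = 3 + 2(r12 + r13 + r23).
4. The square root is the article's theoretical SD. It is also the observed SD of the composite. No distributional assumption was used and no outside value entered.

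**Numerical check.** There were 2,000 simulated datasets per scenario, N = 56.

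| Scenario | Largest absolute difference, theoretical vs observed SD |
|---|---|
| Uncorrelated scales | 7e-16 |
| Common r = 0.3 | 9e-16 |
| Common r = 0.7 | 9e-16 |
| Negatively correlated scales | 9e-16 |
| Unrelated variables (exponential, binary, Cauchy) | 9e-16 |

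All are floating-point rounding.

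**Where the information lies.** For an assumed common correlation r, the SD is sqrt(3 + 6r) and the standardised alpha of the three Z-scores is 3r/(1 + 2r).

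| Assumed r | SD, theoretical and observed | Standardised alpha |
|---|---|---|
| 0 | sqrt(3.0) = 1.73 | 0 |
| 0.3 | sqrt(4.8) = 2.19 | 0.9/1.6 = 0.56 |
| 0.5 | sqrt(6.0) = 2.45 | 1.5/2.0 = 0.75 |
| 0.7 | sqrt(7.2) = 2.68 | 2.1/2.4 = 0.875 |

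Internal consistency runs from none to high down the table, while the comparison of the two SDs passes in every row.

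**When the two SDs can differ.**

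- *Different participants on each side.* With an assumed 10% missing per scale, an assumed common r of 0.5, Z-scores from available cases and pairwise correlations, observed minus theoretical SD had mean −0.005 and SD 0.10, with a largest absolute value of 0.47.
- *Baseline composite scaled by Day 3 SDs.* If every baseline SD is c times its Day 3 SD, the observed SD is c × sqrt(3 + 2(r12 + r13 + r23)). With an assumed r of 0.5 and c = 0.8, 1.2 or 1.5, the observed SD is 0.8 × 2.45 = 1.96, 1.2 × 2.45 = 2.94 or 1.5 × 2.45 = 3.67, against a theoretical 2.45.

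The first gap reflects which participants are counted and the second a change in spread. Neither bears on construct validity.

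**The case against.** Five points can be made for the plan.

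- **Agreement is not strictly guaranteed.** It needs the SDs, correlations and composite to come from the same complete participants. The article does not say whether standardisation precedes or follows imputation, and the identity does not carry over to the baseline composite. This is right, and the verdict is limited accordingly. It does not help the plan: such a disagreement would be a data-handling artefact that the stated purpose invites readers to take as poor validity.
- **Nothing depends on the check.** There is no threshold and no gate to the ANCOVA, so the estimate, p-value, type I error and sample size are untouched. This stands and limits the severity. The plan still commits the report to a conclusion that has not been tested.
- **Weakly related scales would be visible.** The formula needs the three correlations, so a reader who saw them would notice. This stands as far as it goes, but the article bases its inference on the match of the SDs, not on the size of the correlations.
- **Component results are already planned.** PSS-10, GAD-7 and PHQ-9 are each modelled over time including Day 3, and secondary results are to carry estimates and 95% confidence intervals. This is partly right. However, between-group comparisons at each time point follow only if the group-by-time interaction is significant. A benefit present by Day 3 and then sustained need not produce one.
- **Further validation analyses are a preference.** Deleting the claim alone would cure the error. That is so; they are needed only if the trial wishes to claim validity.

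**Conclusion.** The concern holds. For the Day 3 composite as defined in section 2.6, the theoretical and observed SDs are one number computed two ways, and their agreement cannot confirm construct validity. The identity is exact when both sides use the same complete participants and the same divisor. It therefore holds within each imputed dataset if standardisation is done there.

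The damage is to interpretation only: an unsupported validity statement attached to the sole primary outcome. The primary ANCOVA is not affected. The article fixes the formula, the comparison and the inference, and a separate analysis plan could not turn an identity into a test of validity. The point should be corrected before analysis, but it does not threaten the trial.

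**What to change.** In section 2.6, item (3), delete the statement that the comparison confirms construct validity, or relabel the step as a computation check on the Day 3 composite, run within each completed dataset.

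If support for the composite is wanted, prespecify three items: the three inter-scale correlations, the internal consistency of the three Z-scores, and the correlation of the composite with IES-R and PSQI at baseline. Table 3 shows that both are collected on Day 1.

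Report the Day 3 group differences on PSS-10, GAD-7 and PHQ-9, with 95% confidence intervals, beside the composite result, whether or not the group-by-time interaction is significant.

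The cost is one sentence removed or reworded and one table added from data already planned. No new measurements, participants or design changes are needed.
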